
### Randomization

We randomize parents in a 1:1 ratio to receive either PATHS or control at the start of the study; following the 6-month assessment, parents initially randomized to the control group are given PATHS. Initial random assignment is stratified by sons’ report of sexual risk (any vs no prior condomless anal or vaginal sex [CAVS]) and race or ethnicity (non-Hispanic White vs other racial or ethnic backgrounds) and blocked in groups of 20.

### Treatment Conditions

Participants assigned to the intervention condition receive both Lead With Love (LWL) and PATHS after randomization. Participants initially assigned to the control condition receive only LWL.

#### Lead With Love

LWL is a 35-minute “education entertainment” film-based intervention we developed to provide parents with a lesbian, gay, or bisexual child with general support, information about sexual orientation, and behavioral guidance for supporting their child (unrelated to HIV) [21]. Pre- and postdata from parents who view LWL suggest that parents feel greater self-efficacy for being a good parent to a lesbian, gay, or bisexual child after viewing the film [21].

#### Parents and Adolescents Talking About Healthy Sexuality

We developed PATHS through an iterative process involving review of existing theory and empirical research, collecting primary qualitative data from parents and youths, and collaborating with parents to create the intervention content.

Existing theory about why parents communicate about sex largely focuses on characterizing barriers to doing so and suggests that interventions must address these barriers to be effective [23,24]. Common barriers include parent discomfort and embarrassment, lack of knowledge of technical aspects of sex, fears of encouraging sex, low self-efficacy to communicate, and concerns about how the child will react and whether communication will matter. No existing theory thoroughly describes parents’ approach-oriented motivations for discussing sex with adolescents, but some suggest applying the integrated behavioral model [18], which we adopted to guide this intervention. When applied to communication, the model broadly suggests that parents discuss sex with their children when parents have intentions to do so, appropriate skills, and limited barriers. Intentions should be driven by self-efficacy to communicate, favorable attitudes toward communication, and positive expectations for how conversations will go. Figure 1 depicts the conceptual model underlying the intervention.

**Figure 1 figure1:**
[figure not shown]
PATHS conceptual model. GBA: gay and bisexual adolescent; PATHS: Parents and Adolescent Talking About Healthy Sexuality; PrEP: pre-exposure prophylaxis.

To further understand families’ experiences with communicating about sexuality and HIV, we conducted qualitative interviews and focus groups with families. Using these qualitative data as a foundation, together with content from sexual health communication interventions for parents of heterosexual youths, we developed PATHS in collaboration with a volunteer Board of Family Experts, comprised of 4 parents of AMSM and 6 AMSM. Once a working version of the intervention had been developed, it was tested for usability and clarity with 6 parents of AMSM.

PATHS was developed with the goal of changing the following parent behaviors: (1) to increase the overall frequency and quality of parent-adolescent communication about sex and HIV, including communicating about condoms and pre-exposure prophylaxis (PrEP) as means to prevent HIV; (2) to support parents teaching their sons the proper mechanics of condom use; (3) to help parents enable their sons’ access to condoms; and (4) to assist parents in facilitating HIV testing for their sons. These behaviors, in turn, are hypothesized to increase GBA preparedness for sex and ultimately decrease CAVS that is not protected by PrEP.

Parents access PATHS on any web-enabled device with a unique username and password. PATHS is fully automated, self-paced, and designed so parents can access all content in a single session (lasting 30-60 minutes) or in multiple sessions. Content is divided into seven required modules: (1) welcome and overview, (2) importance of communication, (3) HIV information, (4) using and acquiring condoms, (5) PrEP, (6) HIV testing, and (7) a review with a parent “to-do” list. Optional supplemental modules include content on understanding anal intercourse and what to do if a child tests positive for HIV. These topics were deemed optional because they either did not apply to all youths (ie, what to do if a child tests positive) or because parents might not be ready to receive the material (ie, understanding anal intercourse).

PATHS content focuses on changing the relevant determinants of parent behaviors (Figure 1). Drawing from theory and research pointing to the benefits of multimodal communication [25,26] that includes both peer and expert-delivered messages [27-29], content is communicated via a combination of narrated text pages, animated videos, and videos integrating experiences of real parents, GBA, and adolescent health experts. Video content applies multiple principles of social learning theory [30,31]. To increase parents’ perceived similarity to and identification with the “cast” depicted in the videos, we feature brief personal stories in which our parents and experts describe common experiences others might relate to (eg, a parent sharing their experience of a child coming out or an expert mentioning that they are also a parent). Additionally, the cast is weighted with racial or ethnic minority representation—75% (3/4) of the adolescent health experts are people of color, and over half of the parents or youths depicted are people of color. In addition, consistent with social learning principles, parents in the videos describe their experiences engaging in intervention-recommended behaviors in ways that emphasize both their persistence in the face of barriers as well as the ultimate rewards they gleaned from engaging in the behavior.

Because goal-setting is an effective component of many behavioral interventions [32], each required module was followed by an interactive activity encouraging parents to select how they planned to follow up with their son about the content. Recognizing that parents and sons approach these discussions about sexuality with different degrees of experience and comfort, we suggest 3 different options for how to engage with their son about each segment of the content. The options vary in intensity or complexity and, presumably, in the degree to which the interaction will be impactful for their son. We categorize the options as “good,” “better,” and “best” and inform parents that taking any of the recommended actions will help their son reduce his HIV risk. For example, in working with parents to teach their sons the proper mechanics of condom use, we give parents the following three options: (1) forward an instructional video to your son via the web application with a personalized note (good); (2) forward the video, watch it with your son, and discuss it (better); or (3) do a condom demonstration together with your son (best). The intervention allows parents to facilitate some of these interactions by directly forwarding certain content (eg, videos and fact sheets) to their sons’ mobile numbers or email addresses. Once parents select the option they want to pursue, a personalized to-do list is populated for them that they can print or email to themselves in the final module.

After initially developing PATHS, we conducted a pilot RCT with 61 parent-adolescent dyads. Results found that PATHS increased both parent and child reports of how much parents discussed HIV, provided instruction on condom skills, helped sons access condoms, and facilitated their sons in getting HIV tests [20]. In total, 96% (30/31) of parents in the pilot trial indicated that they were “very” or “extremely” satisfied with PATHS, that it was easy to use, and the content credible. The intervention did not increase family conflict as reported by either parents or adolescents.

#### One-Month Refreshers

One month after completing the initial intervention assigned, parents are invited to revisit the PATHS web application to complete a “refresher” session designed to reinforce the intervention messaging. The refresher used in this trial was newly developed after the initial pilot RCT of PATHS.

For parents assigned LWL alone, the refresher consists of a series of text pages that summarize the important messages and guidance provided in the original film. For parents assigned PATHS, the refresher first asks parents whether they have been able to successfully engage in each of their selected interactions with their son (ie, the activities they chose to put on their “to-do” list). If a parent indicates that they have not achieved their goal in the previous month, they are presented with a list of possible barriers or reasons why completing the activity was difficult for them. After parents select the barriers they experienced, they are provided with content tailored to each selected barrier designed to help the parents navigate the particular challenge. Once parents review that content, they have the opportunity to reset the goals they did not achieve. Parents also receive reinforcement for any goal they did successfully achieve. Goals that were achieved at the “good” or “better” level are reinforced, and parents are given the opportunity to also set a new goal and achieve the “best” status for a given activity (eg, if they previously just forwarded the condom instruction video to their child, they are asked if they would like to try doing a physical condom demonstration with their child). All new goals that parents set for themselves are recorded on a refreshed to-do list that parents can print or email to themselves.

#### Postintervention Nudges

After parents complete different intervention activities, the application automatically sends brief messages to them via text or email to motivate them to engage in behaviors recommended by PATHS (or behaviors recommended by LWL, for participants assigned to the control). Messages are sent 1 week after completion of the initial intervention modules and then again 1 and 2 weeks after completion of the refresher module. For participants who fail to complete an intervention activity, messages are sent at the same intervals, but timed according to when the activity no longer became available to them.

### Assessment Schedule

The schedule of study activities and assessments by participant and condition is summarized in Figure 2.

**Figure 2 figure2:**
[figure not shown]
Schedule of activities by participant and condition. GBA: gay and bisexual adolescent; LWL: Lead with Love; PATHS: Parents and Adolescent Talking About Healthy Sexuality. Color coding distinguishes types of study events: intervention activities, assessments, and randomization/crossover procedures.

### Outcome Considerations

Determining the appropriate sexual health outcomes for this intervention trial requires balancing the needs for methodological rigor, feasibility, and developmental appropriateness for the younger adolescents in our study. The primary outcomes for most trials of HIV prevention interventions overwhelmingly fall into two categories: (1) self-reported sexual risk behaviors (eg, condomless intercourse) or (2) biological (eg, laboratory tests for sexually transmitted infections [STIs]). While the rationale for using these outcomes with some populations is strong, they might be less appropriate for adolescents. For example, HIV and STI incidence estimates among younger GBA suggest that powering a trial to detect group differences in these outcomes would require enrolling prohibitively large samples and/or extremely long follow-up periods [33,34]. Moreover, incident STIs and condomless intercourse are of limited utility as outcomes if our hope is to understand intervention effects on youths who have yet to have their sexual debut and who might not have their debut during the study follow-up period.

To address these challenges, we adopt the concept of sexual preparedness (sometimes also referred to as “sexual competence”) [35-38], which is generally defined as the degree to which adolescents have the skills and material resources necessary to engage in sex in a manner that maximizes positive outcomes and minimizes risk. Since PATHS is primarily an HIV-prevention intervention, we focus on those elements of preparedness most relevant to reducing HIV risk: having access to condoms, having the skills to use condoms, intending to use condoms for intercourse, and being “current” on HIV testing, given their level of sexual activity (ie, if not yet sexually active, having had at least 1 experience with testing to understand the process; or if sexually active, having had 1 test in the last year, per Centers for Disease Control and Prevention guidelines). We then use multiple means of assessing these outcomes to increase rigor. Other elements of sexual preparedness (eg, having sexual skills necessary to bring pleasure to oneself or partner and understanding when sex is right for you) might be improved by our intervention (eg, PATHS has content for parents on discussing values with your child as well as information on how to engage in anal sex pleasurably). However, given the limited time we have to engage parents and the importance of sexual risk reduction, those aspects of preparedness are not a primary focus.

Because PrEP is currently clinically indicated only for some adolescents (ie, those who are already sexually active) [39], and because the barriers to PrEP uptake among GBA are numerous and extend well beyond the level of parent influence [40], actual PrEP uptake is not a goal of the intervention at present. Rather, we hope to increase parent and GBA awareness of PrEP, as well as favorable attitudes toward PrEP as an option to consider for sexually active GBA. These outcomes correspond to the first step in the PrEP HIV prevention cascade, which requires that individuals have knowledge of a prevention option and be motivated to use it [41].

Finally, the best measures of behavioral risk for HIV among GBA are still self-reports of sexual behavior obtained with well-tested, developmentally appropriate measures, which we use for this trial [42,43].

### Primary Outcomes

Primary outcomes include GBA’s access to condoms, skills for using condoms, current HIV testing experience appropriate to their level of sexual activity, awareness of PrEP, positive attitudes toward PrEP as a prevention option, intentions to use condoms, and CAVS that is not protected by PrEP. Table 1 summarizes the methods and timing of assessments for each outcome [16,42-51]. CAVS will be assessed using measures developed by Northwestern University’s Institute for Sexual and Gender Minority Health and Well-Being for use with adolescent and young adult MSM [42,43]. The instrument first asks youths about their lifetime sexual experiences broadly (eg, “have you ever done any of the following ...”), and then, directs them to questions that follow up on their experiences (ie, participants with limited sexual experience get questions about kissing and touching and participants with anal or vaginal sexual experience get detailed questions about condom use). This ensures that all participants receive roughly the same number of questions, even if they are less sexually experienced, thereby disincentivizing participants from learning the skip patterns over repeated assessments and misreporting to shorten assessments. Participants who report anal or vaginal sexual experience are queried about the number of partners during the previous 3 months with whom they engaged in anal or vaginal sex with and without a condom. Additionally, participants report detailed information about their 3 most recent anal or vaginal partners (eg, how many times they engaged in receptive anal sex with that partner, with and without a condom). GBA are also queried about their PrEP use, and if they report taking PrEP throughout the previous 3-month period, without missing more than 3 doses a week [52], they are included in the “no CAVS” group.

**Table 1 table1:** Measurement and timing of primary outcomes.

Outcome and reporter			Description of measure		Schedule
**Condom access**					
	GBA^a^	Single item asking if the participant has possession of a condom (at home or elsewhere); if yes, a follow-up question requesting the upload of a photo of the condom in the participant’s hand.		BL^b^, 3, 6, 9, 12	
	Parent	Single item asking the parent if they know their son has possession of condoms.		BL, 3, 6, 9, 12	
**Condom skills**					
	GBA	Condom use self-efficacy scale [44].		BL, 3, 6, 9, 12	
	GBA	Condom knowledge test (objective assessment of ability to differentiate correct and incorrect steps in using condoms from a list) [45].		BL, 3, 6, 9, 12	
	GBA	Video-recorded condom demonstration [47-49].		3, 9	
**HIV testing**					
	GBA	Single item asking if ever received HIV test; follow-up item asking date of most recent test.		BL, 3, 6, 9, 12	
	Parent	Single item asking if son ever received HIV test; follow-up item asking the date of the most recent test.		BL, 3, 6, 9, 12	
**PrEP^c^ attitudes and awareness**					
	GBA	Awareness: single item [16]; attitudes: perception of PrEP (1) efficacy, (2) ease of use, and (3) appropriateness for use in sexually active GBA.		BL, 3, 6, 9, 12	
**Condom use intentions**					
	GBA	Intentions to use condoms for anal or vaginal sex. Three items derived from previous research [50,51].		BL, 3, 6, 9, 12	
**Condomless intercourse**					
	GBA	Past 3-month history of sexual behavior. Count of the number of condomless anal or vaginal sex partners while not adhering to PrEP [42,43].		BL, 3, 6, 9, 12	

^a^GBA: gay and bisexual adolescent.

^b^BL: baseline.

^c^PrEP: pre-exposure prophylaxis.

### Mediators of Intervention Effects: Parent Behaviors

PATHS is hypothesized to have its effect on GBA by increasing parent behaviors that are supportive of sexual health. Their measurement is summarized in Table 2.

**Table 2 table2:** Parent behavioral mediators of intervention effects.

Mediator	Reporter	Description of measure	Schedule
Frequency and quality of parent communication about condoms and HIV	GBA^a^	Perception of parents’ communication behaviors over the prior 3 months. Subscale for frequency or specificity of communication. Subscale for quality of communication (ie, how knowledgeable, trustworthy, and honest a parent is in conversations) [17].	BL^b^, 3, 6, 9, 12
Enabling access to condoms	GBA and parent	Guttman scale constructed by asking whether in the previous 3 months, the parent (1) explained to their son where to get condoms, (2) brought condoms home for their son, and (3) took their son shopping to buy condoms together [53].	BL, 3, 6, 9, 12
Teaching condom skills	GBA and parent	Guttman scale constructed by asking whether in the previous 3 months the parent (1) sent the son any written or video information on how to use a condom, (2) discussed with the son how to put a condom on correctly, and (3) demonstrated how to put a condom on correctly [53].	BL, 3, 6, 9, 12
Facilitating HIV testing	GBA and parent	Guttman scale constructed by asking whether in the previous 3 months the parent (1) helped their son schedule an HIV test, (2) drove their son to get an HIV test, and (3) got tested for HIV together with their son [53].	BL, 3, 6, 9, 12
Having informational PrEP^c^ conversation	GBA and parent	In the past 3 months, has the parent shared information with their son about PrEP (yes or no).	BL, 3, 6, 9, 12

^a^GBA: gay and bisexual adolescent.

^b^BL: baseline.

^c^PrEP: pre-exposure prophylaxis.

### Analytic Plan

#### Hypotheses

The specific questions this study proposes to answer are whether PATHS is efficacious in increasing the degree to which GBA are prepared for intercourse and decreasing their engagement in CAVS 6 months after the intervention. We will further test whether intervention effects persist to 1 year after the intervention, and whether they are mediated by increases in parent behaviors that support GBA sexual health. We hypothesize that GBA whose parents receive PATHS will be more prepared for intercourse and will have fewer CAVS partners, relative to GBA whose parents receive only LWL, at 6 months after the intervention; and when control parents crossover and receive PATHS, we will observe similar improvements in that group. We further hypothesize that families originally assigned PATHS will maintain intervention-related gains 1 year after the intervention. Finally, we hypothesize that intervention effects will be mediated by the specific parent behaviors described earlier.

#### Analysis Overview

Hypotheses will be tested using multilevel models (MLMs), which are appropriate for nested designs, and allow us to use a single combined model to test treatment effects at 6 months as well as duration of treatment effects from 6 to 12 months. MLMs are also a recommended method for modeling mediation in randomized clinical trials [54]. We will estimate MLMs using gold standard methods for conducting intent-to-treat analyses and for handling missing data. Separate models will be run for each outcome variable, with estimation methods and distributional assumptions adjusted accordingly (eg, hierarchical generalized MLMs for dichotomous outcomes). We will use recommended methods for controlling type I error in randomized clinical trials with more than 1 outcome of interest by adjusting for our false discovery rate in all analyses [55].

Moderators of intervention effects are of potential public health interest (eg, is the intervention similarly effective across age and/or ethnic groups?). Powering this trial to formally test for differences across all potential moderators was prohibitive. However, given the value in demonstrating that intervention effects are robust across groups, we will explore whether treatment effects observed in the full sample are similar to those we observe in subgroups differentiated by the following variables: GBA age, GBA sexual debut status at baseline, GBA race or ethnicity, and degree of parent engagement in the intervention content.

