### Study Design

We are conducting an RCT of PATHS with a national sample of parent-GBA dyads recruited online (proposed n=350, 50% racial or ethnic minority). Parents will be randomized in a 1:1 ratio to receive either PATHS or an active control, which is a film-based intervention that provides general support to parents of GBA. The study condition is unblinded for both participants and the research team. Parent and child assessments will occur every 3 months over a 1-year period. Primary outcomes will be evaluated at 6 months after the intervention, and then, the control arm will crossover and receive PATHS, and dyads will be followed for another 6 months. This allows us to further test the effects of PATHS in the control arm while simultaneously modeling the longer-term effects at 9 and 12months in the original intervention arm.

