## Results

The study was funded in March 2022, and we completed enrollment of 393 parent-GBA dyads in September 2025. We project that all participants will have completed study activities by November 2026, with data analysis and results of the trial forthcoming in the first quarter of 2027.

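### Subgroup consistency is to be judged against the full sample that contains each subgroup, which understates differences between groups and cannot demonstrate robustness

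*Protocol article*

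**What the plan says.** The second paragraph of the Analysis Overview first asks whether the intervention works equally well across groups such as age or ethnicity, which is a between-group question. It then concedes the limit on power: "Powering this trial to formally test for differences across all potential moderators was prohibitive". It goes on to describe what will be done instead. The team will "explore whether treatment effects observed in the full sample are similar to those we observe in subgroups", and the reason given is "given the value in demonstrating that intervention effects are robust across groups".

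The subgroup variables are "GBA age, GBA sexual debut status at baseline, GBA race or ethnicity, and degree of parent engagement in the intervention content". The article describes the work as exploration. It names no treatment-by-moderator interaction, no contrast of one subgroup with another, and no criterion for similarity.

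**The concern.** The question is between groups, but the named comparison is part against whole. A subgroup contributes to the full-sample estimate in proportion to its size, so the two numbers are pulled together by construction, and more strongly the larger the subgroup.

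The article also fixes the conclusion the comparison is meant to serve, namely robustness, in the same place where it says formal tests could not be powered. Low power is a reason to report the difference with its uncertainty and to withhold a robustness statement. It does not make apparent similarity informative.

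The stake is the secondary reporting of the trial. PATHS could be described as working similarly before and after sexual debut, or across age or racial and ethnic groups, when the data are compatible with little or no effect in one of them. Debut status matters most here: under Potential Implications of Findings the authors themselves consider it plausible that effects differ by sexual experience.

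**Working it through.** The article gives no alpha, SD, effect size or power for the moderator analysis, so there is no figure of its own to reproduce.

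**Inputs from the article**
- Planned size and one subgroup share: "proposed n=350, 50% racial or ethnic minority" (Study Design).
- Enrolled size: "we completed enrollment of 393 parent-GBA dyads in September 2025" (Results).
- Allocation: "Parents will be randomized in a 1:1 ratio to receive either PATHS or an active control" (Study Design).

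**Assumptions**
- Two-sided alpha 0.05, one continuous outcome with SD 1, no attrition, and no precision gain from repeated measures.
- Treatment arms balanced within subgroups.
- Subgroup share p. The article gives a target near 0.5 for race or ethnicity and no shares for the other variables.

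**Step 1: dilution.** Let d1 be the effect in the subgroup and d2 the effect in the rest.
- Full effect = p·d1 + (1 − p)·d2.
- Subgroup minus full = (1 − p)·(d1 − d2).

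The visible share of the true difference is 50% at p = 0.5, 30% at p = 0.7 and 20% at p = 0.8. For mean differences this needs no assumed effect size.

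**Step 2: illustration, N = 393, p = 0.5, effects 0.5 and 0.**
- Full-sample effect = 0.5·0.5 + 0.5·0 = 0.25, so each half differs from it by 0.25.
- SE full = 2/√393 = 0.101.
- SE half = 2/√196.5 = 0.143.
- SE interaction = 0.101·√(1/0.5 + 1/0.5) = 0.202.
- SE of subgroup minus full = √(0.143² − 0.101²) = 0.101.
- Half-width of the subgroup 95% CI = 1.96·0.143 = 0.280.
- P(the no-effect half's CI contains the full-sample estimate) = Φ((0.280 − 0.25)/0.101) ≈ 0.62.
- Interaction power = Φ(0.5/0.202 − 1.96) ≈ 0.70.

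Under a CI-overlap reading, that half therefore looks consistent with the whole in about 62% of trials, whereas the interaction misses the gap in about 30%.

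**Step 3: other shares, N = 350, true gap 0.6 SD.**

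| Share p | Visible gap | Full estimate inside subgroup CI | Interaction power |
|---|---|---|---|
| 0.2 | 0.48 | 48% | 61% |
| 0.3 | 0.42 | 41% | 73% |
| 0.5 | 0.30 | 49% | 80% |
| 0.7 | 0.18 | 84% | 73% |
| 0.8 | 0.12 | 98% | 61% |

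A simulation of 200,000 draws at p = 0.5 gave a mean gap of 0.300 against the full sample and 0.600 between subgroups.

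**Step 4: smaller gap.** With a 0.3 SD gap, N = 350 and p = 0.5, the interaction SE is 4/√350 = 0.214 and power is Φ(0.3/0.214 − 1.96) ≈ 0.29. The full estimate lies inside the subgroup CI 91% of the time. The gap detectable with 80% power is about 0.60 SD (0.565 at N = 393).

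**The case against.** The strongest reply is that one summary sentence is being read as a decision rule. The article says only that similarity will be explored. It sets no overlap rule or threshold and does not exclude an interaction term, and the details may be in an analysis plan that is not shown. This stands in part: the missing interaction model, intervals and display are not faults in a condensed article. What remains is what the article does fix, namely the full sample as comparator and robustness as the thing to be shown.

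A reader might infer that the plan hides real differences. The documents do not support that. Effects would probably be shown for each level of a variable, so an effect near 0.5 beside one near 0 would be visible. Moreover, if the overlap between the two estimates is handled correctly, the subgroup-minus-full test has the same z as the interaction (0.25/0.101 = 0.5/0.202 ≈ 2.48). The loss arises only when similarity is judged by eye, by CI overlap, or as if the estimates were independent.

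A reader might also infer that the trial makes an unearned robustness claim, or that robustness is the default finding. No such claim appears. Robustness is given as a motive, the low power is stated openly, and the discussion allows for different effects by sexual experience.

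Finally, the size of the problem depends on a scenario and a CI rule supplied here. Several primary outcomes are yes/no or counts, attrition is ignored, and the interaction is itself weak for modest gaps. All of this is correct and limits the point to a minor one.

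**Conclusion.** The point holds as a minor weakness of an exploratory analysis. Comparing a subgroup with the sample that contains it shows only (1 − share) of the difference of interest. Informal judgements of similarity therefore lean towards agreement, most strongly for large subgroups. At this sample size, neither that comparison nor a non-significant interaction can demonstrate that effects are robust across groups.

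The dilution factor is algebraic for mean differences. The 62% and 70% figures are illustrations only, and they rest on the scenario in the working and on judging similarity by whether the subgroup CI covers the full-sample estimate. The primary 6-month comparison, the sample size and the randomisation are not affected.

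**What to change.** For the three baseline moderators (age, sexual debut status, race or ethnicity):
- Report the exploratory treatment-by-subgroup interaction estimate with its 95% CI from the 6-month model.
- Show the effects in complementary subgroups side by side, in place of the full-sample comparator.
- Replace the aim of demonstrating robustness with a statement that an inconclusive interaction is not evidence of similar effects.

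Parent engagement with the content arises after randomisation, so it is left out of this list.

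The cost is a change of wording in the analysis plan and one extra model term per moderator, settled before the analysis starts. The downside is wide intervals that will often be inconclusive, which reflects what the trial can say about moderation.
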